### Sample size

2.7

Based on a previous study [14], the median (interquartile range) scores of the questionnaire items will be as follows: “Did you understand the drug cost?” will be 2.5 (1.0–4.0) and 5.0 (4.25–5.00) in the Usual Explanation and ChemoCalc groups, respectively. Whereas, the corresponding scores for “Do you think the drug cost is important when deciding on treatment?” will be 3.0 (3.0–4.5) and 5.0 (4.25–5.0), respectively. At 90% power and a 0.025 significance level, analysis using Mann–Whitney *U* test with Bonferroni correction indicated that the trial would require 47 patients in each group. Therefore, considering a 10% potential withdrawal rate, we aim to enroll 106 patients (53 per group).

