### Study design

2.1

In this ongoing multicenter, randomized controlled open-label phase 3 trial, we aim to evaluate the effect of ChemoCalc on the understanding of patients regarding medical costs. A study flow diagram is shown in Fig. 1. This study was approved by the Nagasaki University Hospital Clinical Research Ethical Committee (registration number 19070801), Japan. Any changes to the trial protocol will be communicated to all investigators, ethics committees, and the trial registry.

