### Randomization

2.4

Patients will be allocated to groups using a stratified block randomization method. Each investigator will assign participants to the intervention or control group using a centralized, remote computer-generated randomizer built in Research Electronic Data Capture electronic data capture system (REDCap). The stratification factors are age (<50 years and ≥50 years) and grade of Comprehensive Score for Financial Toxicity (COST) tool (grade 0 and grade 1 or higher) [15,16]. There will be an intervention-to-control ratio of 1:1.

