### Trial endpoints

2.6

•Primary endpoint

The primary endpoint will be the comparison of scores of two key questions in the questionnaire between the two groups: “Did you understand the drug cost in today's discussion?” and “Do you think the drug cost is important when deciding on treatment?“. The questions will be rated on a five-point scale, with 1 being “not at all” and 5 being “very much."•Second'ary endpoints1.A comparison of the scores of other questions in the questionnaire (Table 1).2.A comparison of the discrepancy between physician-recommended and patient-selected treatments between the two groups (the patient-selected treatment in the Usual Explanation group is that selected before providing ChemoCalc information). Before discussion with patients, the physicians will register treatment plan ranking using REDCap. Any discrepancy will be judged based on whether the physician's first recommended treatment is selected. If there is a discrepancy, we will investigate whether the treatment choice is more expensive, equal, or less expensive than the first recommended treatment.3.A comparison of discussion time between the two groups. Discussion time is defined as the duration of one interview to discuss the treatment plans.4.The relationship between COST grade and patient-selected treatment. We will categorize the treatments chosen by patients and the first recommended treatments by the physicians into groups with and without discrepancies. In both groups, we will divide treatments selected by patients into three groups: higher, equivalent, and lower than the first recommended treatment by the physician. We will then examine whether it is related to the COST grade.5.The relationship between the upper limit of out-of-pocket costs and patient-selected treatment. We will divide the treatments chosen by patients and the first recommended treatments by the physicians into groups with and without discrepancies. In both groups, we will divide treatments selected by patients into three groups: higher, equivalent, and lower than the first recommended treatment by the physician. We will then examine whether it is related to the upper limit of out-of-pocket costs.

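### The two primary questions are tested by plain Bonferroni, which is valid, but Holm would give more power at the same error rate and sample size

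*Protocol article*

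**What the plan says.** Section 2.6 of the protocol article sets two questionnaire items, understanding of drug cost and importance of drug cost, as primary: "The primary endpoint will be the comparison of scores of two key questions in the questionnaire between the two groups". Each is scored on a five-point scale.

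Section 2.7 sizes the trial "At 90% power and a 0.025 significance level", and reports that the Mann–Whitney "test with Bonferroni correction indicated that the trial would require 47 patients in each group". The assumed medians (interquartile ranges) are, for understanding, "will be 2.5 (1.0–4.0) and 5.0 (4.25–5.00) in the Usual Explanation and ChemoCalc groups, respectively", and for importance, "will be 3.0 (3.0–4.5) and 5.0 (4.25–5.0), respectively". Enrolment follows from "considering a 10% potential withdrawal rate, we aim to enroll 106 patients (53 per group").

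Section 2.9 names the Mann–Whitney test for quantitative variables but no multiplicity correction. Section 2.1 gives the aim as understanding of costs. Section 3 separately justifies importance as a key endpoint.

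**The concern.** With two primary tests, Bonferroni holds each question to 0.025 whatever happens on the other. Holm relaxes the second test to 0.05 once the first has succeeded and still keeps the familywise error at 5% under any correlation between the questions. Bonferroni therefore gives up power on the second question without gaining any error control. Section 2.7 expects an effect on both questions, which is the situation in which Holm gains most. What is at stake is a few points of power per question, and a larger amount for showing both.

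**Working it through.** **Inputs.** Two questions (section 2.6); 0.025 per question, 90% power, 47 per group, 10% withdrawal (section 2.7); 1:1 allocation (section 2.4). Not given and therefore assumed: two-sided tests, and a correlation ρ between the two test statistics of 0 to 0.6.

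**The plan's own figures.**
- Alpha: 0.05/2 = 0.025. Reproduced.
- Withdrawal: 47/0.90 = 52.2, rounded up to 53 per group, 106 in total. Reproduced.
- The 47: medians and quartiles do not fix P(X>Y) on a five-point scale, so no single n follows from them. The tie-corrected Mann–Whitney formula is n per group = T(z₀.₉₈₇₅ + z₀.₉₀)² / [6(p − 0.5)²], where p is P(X>Y) with ties counted half and T = 1 − Σ(pooled proportion)³. Five-point distributions that match the stated quartiles give about 9 to 48 per group for understanding and 16 to 73 for importance. The stated 47 lies inside both ranges and cannot be called wrong. The stated 90% at 0.025 is therefore taken as the planning basis below.

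**Power of a single test.** Non-centrality δ = z₀.₉₈₇₅ + z₀.₉₀ = 2.241 + 1.282 = 3.523.
- At 0.025: Φ(3.523 − 2.241) = 0.900.
- At 0.05: Φ(3.523 − 1.960) = Φ(1.563) = 0.941.

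**Both questions, ρ = 0, by hand.**
- Bonferroni, both: 0.900² = 0.810.
- Holm, both: both tests pass 0.05 and at least one passes 0.025, so 0.941² − (0.941 − 0.900)² = 0.8855 − 0.0017 = 0.884.
- Holm, one given question: 0.900 + (0.941 − 0.900) × 0.900 = 0.937.
- At least one, either method: 1 − (1 − 0.900)² = 0.990.

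**Across the correlation range** (bivariate normal, 90% per question at 0.025):

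| | ρ = 0 | ρ = 0.3 | ρ = 0.6 |
|---|---|---|---|
| Per question, Bonferroni | 90% | 90% | 90% |
| Per question, Holm | 93.7% | 93.3% | 92.9% |
| Both, Bonferroni | 81.0% | 82.2% | 83.9% |
| Both, Holm | 88.4% | 88.9% | 89.7% |
| At least one, either method | 99.0% | 97.8% | 96.1% |

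**If the two questions are unequally powered.** Section 2.7 gives different assumptions for the two questions and a single n, so one may have more than 90%. With 99% on one and 90% on the other, power for both is 89–90% under Bonferroni and about 94% under Holm. The gain is then 4–5 points instead of 6–7.

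**The case against.** The strongest case for leaving the plan alone is that Bonferroni is valid, pre-specified and consistent with the sample size. Its test, alpha and correction agree with one another, the stated 90% per question is kept, and Holm adds nothing to the chance of a first success. All of that stands: this is a missed efficiency, not an error. Bonferroni also comes with simple matching confidence intervals. That is true, but the article plans tests, medians and interquartile ranges and mentions no such intervals, so little is lost. The size of the gain is also uncertain, because the 47 cannot be traced to one pair of distributions.

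A reader might go further and infer that a difference on importance alone would be taken as proof that ChemoCalc helps patients understand costs, since section 2.1 says "we aim to evaluate the effect of ChemoCalc on the understanding of patients regarding medical costs". The document does not support that. No section treats a result on importance as evidence of understanding, and section 3 defends importance in its own right. Nor would Holm prevent such a reading: if only importance had the planned effect, it would still succeed in about 90% of trials.

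A reader might also take the singular wording in section 2.6 to mean that both questions must succeed, so that 90% overstates the power for success. That is only one reading, and the alpha split in section 2.7 points to each question standing alone. A fuller success rule may be in the analysis plan, which is not shown, so its absence from a condensed article is not a fault.

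**Conclusion.** The point holds as an improvement at almost no cost. Holm dominates plain Bonferroni for these two questions: same 5% familywise error, same sample size, about 3–4 points more power per question and 6–7 points more for showing both. These gains rest on the stated 90% per question at 0.025, two-sided tests and correlations of 0 to 0.6, and they shrink if one question is better powered. They do not extend to the chance of at least one significant question. The present plan remains valid if nothing is changed.

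**What to change.** In section 2.7, replace the plain Bonferroni test by Holm at two-sided familywise 0.05: compare the smaller of the two Mann–Whitney p-values with 0.025 and, only if it is significant, the larger with 0.05. Add the same rule to section 2.9, where there is no correction wording to replace. In the same sentence, state that each question supports only its own conclusion.

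Keep 47 per group for analysis and 53 enrolled. The calculation at 0.025 stays valid and is slightly conservative for each question under Holm.

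The cost is more than a wording change. The trial is open-label and had recruited 36 patients by April 2020 (section 2.10), so this needs a dated amendment made before unblinded data are seen, and section 2.1 commits the trial to telling investigators, ethics committees and the registry. Simple matching Bonferroni confidence intervals are given up, but the article does not plan to report them.

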### Data management

2.8

Registration of patients and data management will be carried out using REDCap. Only the principal investigator, subinvestigators, and research collaborators, registered at the research secretariat will be able to access REDCap to enter and modify data. The original questionnaire will be submitted to Nagasaki University Hospital and the data will be provided a study code; blinded data will be analyzed. All data will be discarded 5 years after completion of the study.

### Statistical analyses

2.9

Analyses of the primary and secondary outcomes will be based on intent-to-treat and full analysis sets, which will include withdrawal from the study. Patients' clinicopathological features will be compared between the intervention and control groups. Variables will be presented as frequency (for categorical variables) and as median and interquartile range (for quantitative variables). Fisher's exact test will be used to assess associations between categorical variables, and *[Wilcoxon's rank sum test]* Mann–Whitney *U* test will be used to assess quantitative variables. All statistical analyses will be performed using SAS, EZR, and JMP software programs.

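### The primary test ignores the age and COST-grade strata used in randomisation; it stays valid, but is conservative and less efficient if those strata predict the answers

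*Protocol article*

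**What the plan says.** Three places in the protocol article bear on this.

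- **Section 2.4, Randomization:** "Patients will be allocated to groups using a stratified block randomization method". "The stratification factors are age (<50 years and ≥50 years) and grade of Comprehensive Score for Financial Toxicity (COST) tool", the latter split into grade 0 against grade 1 or higher. That makes four strata. Allocation is equal: "There will be an intervention-to-control ratio of 1:1".
- **Section 2.7, Sample size:** the calculation is set "At 90% power and a 0.025 significance level", and the Mann–Whitney U "test with Bonferroni correction indicated that the trial would require 47 patients in each group". For the understanding question, the assumed medians and interquartile ranges "will be 2.5 (1.0–4.0) and 5.0 (4.25–5.00) in the Usual Explanation and ChemoCalc groups, respectively".
- **Section 2.9, Statistical analyses:** the Mann–Whitney U "test will be used to assess quantitative variables". The primary scores fall under this sentence, since Section 2.6 states "The questions will be rated on a five-point scale".

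No stratified or adjusted analysis is named anywhere in the article. It also gives no figure for how strongly age or COST grade is related to either score.

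**The concern.** Blocking within strata makes the arms nearly equal on age group and COST grade. If those factors predict the score, the true variability of the between-arm comparison is smaller than under simple randomisation. A pooled rank test does not know this: it counts the between-stratum spread as noise and uses too large a variance. Its real type I error then lies below the nominal 0.025, and it detects a true difference less often than a test that compares patients within strata.

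At stake is efficiency, in a trial that tests each of two questions at 0.025 with 47 evaluable patients per arm. There is no risk of an inflated false-positive rate.

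**Working it through.** **1. The plan's own figures.** Withdrawal: 47 / 0.9 = 52.2, rounded up to 53 per group and 106 in total, as stated. The 47 cannot be derived uniquely, because medians and quartiles do not fix P, the probability that a ChemoCalc score exceeds a control score (ties counted half). Noether's formula, n = (z₁₋α/₂ + z₁₋β)² / [6(P − 0.5)²], with two-sided 0.025 and 90% power gives (2.241 + 1.282)² / (6 × 0.21²) = 12.41 / 0.2646 ≈ 47 at P = 0.71. So 47 is attainable but not verifiable. For distributions fitted to the stated quartiles, the plain test at 47 per arm had 95–100% power.

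**2. Assumptions the article does not supply.** Two-sided testing (sidedness is not stated), blocks of 4, stratum prevalences and the strength of the strata effects. The last is varied from nil to strong.

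**3. Logit model.** 94 evaluable patients, 75% aged 50 or over, 50% COST grade 1 or higher, proportional-odds treatment effect of 1.5 logits. Share of latent variance due to strata = b²(0.75 × 0.25 + 0.5 × 0.5) / [b²(0.4375) + π²/3], where b is the effect per factor. For b = 1 this is 0.4375 / 3.727 = 12%; for b = 1.5 it is 0.984 / 4.274 = 23%.

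| b per factor | Size, plain | Size, van Elteren | Power, plain | Power, van Elteren |
|---|---|---|---|---|
| 0 | about 0.025 | about 0.025 | 95.9% | 95.5% |
| 1 | 0.015 | 0.022 | 94.1% | 95.6% |
| 1.5 | 0.012 | 0.025 | 89.5% | 94.5% |

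A separate run of the same design gave a plain-test size of 0.010–0.011 against 0.026 at b = 1.5. The power forgone was 5–6 points at b = 1.5, about 2 at b = 1, and under 1 point either way at b = 0 or 0.5.

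**4. Check with a second model.** Normal latent scale, 30% in one age stratum, 50% in one COST stratum, treatment effect 0.78 latent SD (chosen so that the plain test has about 90% power). R² is the share of latent variance explained by the strata; ranges cover the two questions.

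| R² | Size, plain | Size, van Elteren | Power, plain | Power, van Elteren |
|---|---|---|---|---|
| 0 | 0.022–0.026 | 0.023–0.025 | 88–89% | 88–89% |
| 4% | 0.019–0.022 | 0.022–0.024 | 88–90% | 88–90% |
| 10% | about 0.016 | 0.022 | 89–91% | 91–92% |
| 23% | 0.012 | 0.025–0.026 | 89–91% | 93–95% |
| 32% | about 0.010 | about 0.025 | 91–92% | 96–97% |

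Monte Carlo error is about 0.002 for size and 0.005 for power. The approximation size = 2[1 − Φ(2.241 / √(1 − R²))] gives 0.022, 0.018, 0.011 and 0.007 for the last four rows: the same direction and a similar order.

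**5. At the planning effect.** The control upper quartiles in Section 2.7 are 4.0 and 4.5, so roughly 25% or fewer controls score 5. The ChemoCalc lower quartile is 4.25 for both questions, so roughly 75% score 5. The log odds ratio at that cut is about ln[(0.75/0.25) / (0.25/0.75)] = ln 9 = 2.2. With 2.2 logits, both tests exceeded 99.6% power at every strata effect from 0 to 1.5 logits and differed by at most 0.2 points. In the second model, at 1.3 latent SD, both exceeded 99.8%.

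**The case against.** The strongest case against the point is that nothing here is wrong. The sizing test and the analysis test are the same, type I error stays at or below nominal, and the plain test held about 88–96% power in these runs against a 90% target. A material loss needs two things together: a treatment effect weaker than planned, and strata effects as large as the treatment effect for both age and COST grade. A condensed article may also leave adjusted analyses to a plan that is not shown.

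Most of this stands, and it limits the point to efficiency. It does not remove it, because the article is not silent: it names a specific test, and that test does not use the design.

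Three stronger readings are tempting and unsupported.

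- A reader might infer that the test is too conservative as a matter of fact, or that the trial is underpowered. Both the conservatism and the loss depend on a strength of association that the article does not give, and the sizing already used the unstratified test.
- A reader might infer that COST grade was chosen because it predicts the answers. Section 2.4 gives no reason for either factor. An association with the cost-importance question is plausible, since Section 2.6 plans to relate COST grade to treatment selection; for age and for the understanding question the case is weaker.
- A reader might add that medians at the scale ceiling, without a confidence interval, hide the size of the effect. That is a separate reporting matter, which an analysis plan can supply.

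**Conclusion.** The mismatch between a stratified randomisation and an unstratified primary test is certain; its cost is conditional. If the strata are not prognostic, nothing is lost. At about 10% of latent variance explained, the size falls to about 0.016 and 1–2 power points are forgone; at 23–32%, it falls to 0.010–0.012 and about 4–6 points are forgone, for treatment effects at which the plain test has roughly 90% power. Near the planning effect the choice of test makes practically no difference to power. These sizes rest on the assumed two-sided level, block size, stratum prevalences and strata effects. This is a modest improvement available without cost in patients, not an error in the sample size or a threat to validity.

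**What to change.** Before database lock, state that the primary test for each key question is the van Elteren (stratified Wilcoxon rank-sum) test over the four randomisation strata, at 0.025 per question, and that the unstratified Mann–Whitney U test is a sensitivity analysis.

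The cost is one sentence in the analysis plan. The strata are recorded at randomisation, and SAS, already named in Section 2.9, runs the test as a stratified Cochran–Mantel–Haenszel analysis. No new data or patients are needed and the sample size stands. The only downside is a power change of under 1 point if the strata turn out not to be prognostic.

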### Study status

2.10

Patient enrollment started in July 2019 and 36 patients had been recruited as of April 2020, and the recruitment is ongoing.

## Discussion

3

This will be the first randomized control trial to verify the efficacy of the drug cost estimation software ChemoCalc in assisting patients with advanced breast cancer to select treatments that are more cost effective. Our findings will help identify treatment choice changes under improved cost communication. The American Society of Clinical Oncology established a Cost of Care Task Force in 2009, which developed a Guidance Statement on the Cost of Cancer Care [17]. It stated that patient–physician discussions regarding cost are an important component of high-quality care and that educational and support tools for oncology providers are needed to discuss costs with patients and help guide decision making. Although all institutions participating in this study are certified by the Japanese Breast Cancer Society and all investigators specialize in breast cancer, doctors are specifically educated regarding cost communication. We hope to demonstrate that ChemoCalc is a useful tool for informing patients and explaining drug treatment options.

Patients’ impression regarding the importance of drug cost in making treatment decisions based on high out-of-pocket costs may be associated with medication nonadherence [18]. Among patients with chronic myelogenous leukemia in Japan, approximately 30% considered treatment discontinuation because of treatment-related financial burden [19]. We believe that by improving cost communication between patients and their doctors, patients will be able to judge whether a treatment is economically feasible in advance, ensuring adherence and avoiding treatment discontinuation. Therefore, we aim to assess whether patients consider drug costs to be important as a key endpoint.

Some limitations of the study should be noted. First, because Japan's medical insurance system is unique, the results of this study can only be applied for cost communication between Japanese doctors and patients. However, an understanding of how pre-treatment cost communication affects patient treatment choices should benefit all physicians and patients. Second, our study does not list specific guidelines for these discussions, other than the inclusion or exclusion of ChemoCalc. Few doctors may discuss drug cost during routine medical appointments, but others may not. Because our aim is to investigate whether ChemoCalc changes patients' understanding of drug costs regardless of their assigned physician, we did not standardize the methods by which physicians will present or explain drug cost issues.

In conclusion, in the present study, we will assess a strategy of drug cost communication in Japan and characterize the importance of cost communication in patients with advanced breast cancer.

